**Randomization**

A Randomization plan will be created online on [www.randomization.com](http://www.randomization.com) by a statistician who will not be part of the study. A total of 410 participants will be randomised into a single treatment using randomly permuted blocks method. Small blocks of various sizes will be used so that randomization could less likely be guessed. Patients will randomly be distributed into one of the two groups in a ratio of 1:1. The randomization will be implemented with opaque envelopes.

**Blinding**This study is an evaluator blinded study. The blinding of both participants and healthcare workers is not possible in such type of intervention. Only the patient and the study physician know the randomization outcome. Other team members, patient evaluators and data collectors are blinded. After finishing the study, statistician will be present un-blinded data.

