**Treatment Protocol**

**1. Groups and intervention procedures:**

After signing the informed consent, all patients will be randomly divided into the following two groups: the experimental group will be given the nationally recommended standard drug treatment + ultra-short-wave diathermy treatment; the control group will be given only the nationally recommended standard drug treatment. Each group is planned to include 205 participants.

**Short wave treatment dose:** Ultra-short-wave therapy treatment will be performed through application of ultra-short-wave therapy machine electrodes on the anterior and posterior parts of the trunk for 10 minutes, twice a day for 12 consecutive days.

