**Outcome measures**

The primary outcome measures will be time to positive-to-negative conversion of COVID-19 nucleic acid in pharyngeal swab, in days. The secondary outcome measures include nucleic acid test rate and recovery from symptoms , vital signs assessment, treatment adverse effects, Vital capacity, Oxygen saturation, Computed Tomography(CT), Complete blood count(CBC), Creatine kinase (CK) ,Lactate dehydrogenase (LDH), Pharyngeal swabs RT-PCR, Inflammatory cytokines, Inflammatory Markers (Erythrocyte sedimentation rate ( ESR), C-reactive protein ( CRP ),  Procalcitonin ( PCT )), Immune Markers (CD3, CD4, CD8) and SIRS scale scores measured at baseline, after 7 days, 14 days, 21 days, and 28 days of treatment.

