**Adverse event records, reports and treatments**

**1. Definition of adverse events**

An adverse event is any undesired medical event that occurs during or after treatment to a patient in a clinical study. All adverse events do not necessarily have a causal relationship with the treatment. Since short wave diathermy is routinely practiced for pneumonia treatment in our rehabilitation department, no large scale adverse events have been found in routine treatments of pneumonia.

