Linear regression analysis will be used to evaluate any relationship between age, gender and study groups and the primary (time to positive-to-negative conversion of COVID-19 nucleic acid test) and some secondary variables. Adjusted and unadjusted analysis will be performed. Compliance analysis: Statistics whether the patients were treated with short wave on time. According to the requirements of the adverse reaction correlation, we will list the adverse events and adverse reactions of the two groups (including the number of various adverse events, laboratory testing indicators before and after the treatment "normal to abnormal" or” "Aggravated abnormally"), the number of cases and the rate of change, list the reasons and explain. Chi-square test will be used for statistical analysis of adverse reactions. Within the group and between the groups analysis will be performed using 95% confidence internal and a p value of 0.05. Analysis of influencing factors: If there are significant differences between the two groups before treatment, such as age, gender, disease type, and condition, or there are related factors (such as combined medication) that significantly affect the effects of treatment during the treatment, the comparison of the efficacy, these factors will be considered as covariates, and analysis of covariance or logistic regression will be is used. The analyzed data will mainly be expressed in the form of self-explanatory tables with statements, table notes. The results of repeated measurement data will be expressed in both tables and statistical charts to increase readability.

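### The only safety test the protocol names is on adverse reactions, not all-cause adverse events; with no sham and no blinded causality judgement, it is open to attribution that differs by arm

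*Protocol*

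**What the plan says.** The second paragraph of the Data Analysis Plan keeps two concepts apart: "we will list the adverse events and adverse reactions of the two groups". That sentence opens with "According to the requirements of the adverse reaction correlation", which ties the exercise to a relatedness judgement, although the term is not explained. It also covers laboratory values that worsen, with case counts and rates. The test is then named: "Chi-square test will be used for statistical analysis of adverse reactions".

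The section Definition of adverse events takes events without regard to cause: "All adverse events do not necessarily have a causal relationship with the treatment". Adverse reaction has no definition anywhere. Under Outcome measures, the one safety item among the secondary outcomes is "treatment adverse effects".

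On the arms, Groups and intervention procedures says that "the control group will be given only the nationally recommended standard drug treatment"; no sham is described. On blinding, the protocol says "Only the patient and the study physician know the randomization outcome", while evaluators, data collectors and other team members are blinded. Reporting requirements has unnamed researchers assess each event for seriousness. No section says who judges causality.

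**The concern.** Randomisation protects a comparison of everything that happens to patients after allocation. It does not protect a comparison of the subset that someone has judged to be caused by treatment, unless that judgement is made in the same way in both arms.

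Here the opportunity to be counted is unequal by design. A control patient can have a reaction only to the standard drugs. An experimental patient can have one to those drugs or to diathermy. The same clinical or laboratory change could be a reaction in one arm and only an event in the other, even with careful assessors. Because nothing blinds the causality judgement, knowledge of the arm could add to this.

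At stake is the safety conclusion for a physical treatment added to standard care. A spurious excess would count against it unfairly. A masked excess would give false reassurance, and the protocol already records the expectation that "no large scale adverse events have been found in routine treatments of pneumonia".

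**Working it through.** The protocol states no adverse event rate and no safety power figure, so there is none to reproduce. What follows shows how far the named test can move under assumed rates.

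**Inputs from the protocol.** 205 patients per arm, 1:1 allocation, chi-square test, p value threshold 0.05 (taken as two-sided; the protocol does not say).

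**Assumptions, not in the protocol.** The proportion of patients with an adverse event (10% to 30%) and the probability that an event is attributed to treatment in each arm.

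**Model.** Adverse reaction rate = adverse event rate × probability of attribution.

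**1. One worked data set, equal true event rates.** Assume 20% in each arm: 0.20 × 205 = 41 patients.
- Controls: 20% attributed to drugs, 0.20 × 41 = 8.2, taken as 8.
- Experimental: the same 20%, plus a further 25% or 50% attributed to diathermy: 0.45 × 41 = 18.5 (taken as 18) or 0.70 × 41 = 28.7 (taken as 29).

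Uncorrected test: z = (difference in proportions) / √[p̄(1 − p̄) × 2/205].
- 8 against 18: p̄ = 26/410 = 0.0634, SE = 0.0241, difference = 10/205 = 0.0488, z = 2.03, p about 0.04.
- 8 against 29: p̄ = 37/410 = 0.0902, SE = 0.0283, difference = 21/205 = 0.1024, z = 3.62, p < 0.001.

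The first result is fragile. A continuity correction takes one patient off the difference, so z = 2.03 × 9/10 = 1.82 and p is about 0.07.

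**2. Rejection rate with equal true event rates** (simulation of the uncorrected test, 200,000 runs per scenario).

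| Attribution, experimental / control | Events 10% | Events 20% | Events 30% |
| --- | --- | --- | --- |
| 50% / 50% | 5% | 5% | 5% |
| 50% / 25% | 26% | 48% | 68% |
| 50% / 10% | 70% | 95% | 99% |

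Hand check of the 48%: the reaction rates are 0.10 and 0.05, with p̄ = 0.075. The SE under no difference is √(2 × 0.075 × 0.925/205) = 0.0260; the SE under the alternative is √[(0.09 + 0.0475)/205] = 0.0259. Then Φ[(0.05 − 1.96 × 0.0260)/0.0259] = Φ(−0.04), about 0.48.

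**3. A true excess, 30% against 20%.**
- All-cause events tested: SEs 0.0428 and 0.0425, Φ[(0.10 − 1.96 × 0.0428)/0.0425] = Φ(0.38), power about 65%.
- Reactions tested, attribution 50% in both arms: 15% against 10%, power about 33%.
- Reactions tested, attribution one third in the experimental arm and one half in controls: 10% against 10%, rejection about 5%. The excess disappears.

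**Reading.** With equal attribution the test keeps its error rate and, in the scenario of step 3, loses power. With unequal attribution it can reject far too often or miss a real excess. A test of all-cause events is unaffected by attribution: with equal true rates it stays at about 5%.

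**The case against.** The strongest reply has four parts.

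- **The term is undefined.** The test sentence follows a block on events, reactions and laboratory changes and might be shorthand for all of it. This is possible, but the preceding sentence names events and reactions side by side, and the distinction would be redundant if they meant the same. An undefined term in the only named safety test also needs repair.
- **All-cause data are kept.** This stands. Every event goes on the case report form, serious events are reported whatever their cause, and events and laboratory changes are listed for both groups. A general sentence in the Data Analysis Plan applies chi-square to categorical data between groups and could reach all-cause events. But the specific sentence names reactions, and an analyst would follow it.
- **An analysis plan may settle it.** It may. The point here is not a missing detail but the choice that the protocol does state.
- **The figures come from the assumptions.** This stands in full. The assumed gap in attribution produces the result.

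A reader might infer that the unblinded study physician makes the attribution, so that the test reflects attribution and not harm. The documents do not support this. They say that the physician knows the allocation, but not who judges causality. The test mixes harm and attribution, and is distorted only as far as attribution differs by arm. Nor do they support a predicted direction: unequal opportunity points to over-counting in the experimental arm, while the stated expectation of few problems points the other way.

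**Conclusion.** The concern holds in limited form. The one explicit between-group safety test is placed on adverse reactions, in a design where only one arm receives diathermy, no sham is used and nothing blinds the causality judgement. That comparison is open to differential attribution, which an all-cause comparison by randomised arm would avoid.

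The size cannot be set from the documents. In the assumed scenarios with equal event rates, rejection runs from the nominal 5% (equal attribution) to 99% (50% against 10% attribution, 30% event rate). In the opposite direction, about 65% power for a true excess falls to about 5%. These figures show what is possible, not what is expected. The conclusion rests on reading adverse reaction as the treatment-related subset, which is the natural but not the only reading. The primary efficacy result is not affected, and no all-cause data are lost.

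**What to change.** **Outcome measures.** Replace the item on treatment adverse effects with two: patients with at least one adverse event, and patients with at least one serious adverse event, each regardless of attribution, from baseline to day 28 in both arms.

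**Data Analysis Plan.** Put the chi-square comparison on these two counts, by randomised arm. Define adverse reaction, say who judges relatedness and whether that person knows the arm, and report attributed reactions by arm descriptively, without a test.

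**Laboratory shifts.** Report these by arm descriptively as well. Testing each one would add many comparisons with no multiplicity rule, because the panel is long and is repeated at days 7, 14, 21 and 28.

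**Cost.** Wording only: Reporting requirements already has all adverse events recorded on the case report form. The drawback is that events due to COVID-19 itself add background noise to an all-cause comparison. The descriptive table of attributed reactions keeps the more specific information in view.

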**Data Analysis Plan**

The principles of intent-to-treat analysis will be followed to include all participants randomised for the study. Data normality will be assessed using the Kolmogorov-Smirnov (K-S) and Shapiro-Wilk (S-W) tests. The missing data will be managed by multiple imputations. Descriptive statistics: mean, median, maximum, minimum, confidence interval, and standard deviation will be calculated for continuous data, and frequency distributions will be calculated for categorical data. Prevalence of negative and positive tests will be calculated at specific time points. Independent t test will be used to compare the means after intervention between the two groups in case of normal distribution of data. If the data was not normally distributed Mann Whitney test will be used. Chi-square test will be used for comparison of categorical data between the two study groups.

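### The covariate rule admits medication given during open-label treatment into the efficacy comparison, so the adjusted result is chosen from the data and is not the intention-to-treat effect

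*Protocol*

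**What the plan says.** Under Data Analysis Plan, the paragraph labelled Analysis of influencing factors has two triggers for covariate adjustment of the efficacy comparison.

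- Before treatment: "If there are significant differences between the two groups before treatment, such as age, gender, disease type, and condition".
- During treatment: "there are related factors (such as combined medication) that significantly affect the effects of treatment during the treatment".

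On either trigger, "these factors will be considered as covariates, and analysis of covariance or logistic regression will be is used". Both lists are introduced by examples and are open-ended.

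The same section plans other analyses of the same outcome:

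- An unadjusted comparison: "Independent t test will be used to compare the means after intervention between the two groups in case of normal distribution of data", with Mann-Whitney as the alternative.
- A regression with no condition attached: "Linear regression analysis will be used to evaluate any relationship between age, gender and study groups and the primary" outcome and some secondary ones.
- A general statement: "Adjusted and unadjusted analysis will be performed".
- The analysis principle: "The principles of intent-to-treat analysis will be followed to include all participants randomised for the study".

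On blinding, the Blinding section states: "The blinding of both participants and healthcare workers is not possible in such type of intervention".

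**The concern.** The during-treatment trigger is the serious part. A medicine started after randomisation is not a baseline characteristic. The Background section describes current care as supportive and directed at symptoms, and it includes antivirals and corticosteroids, so prescribing can follow how the patient is doing. Because the physician knows the arm, prescribing can also follow the allocation. Co-medication may then be a consequence of the diathermy, a marker of worsening, or a reaction to knowing the arm. Conditioning on it compares patients who were made alike on something that happened after randomisation. All randomised patients may still be in the model, but the coefficient for arm no longer measures the effect of assignment. The trigger also depends on whether the factor significantly affects the treatment effect, so the outcome data decide the model.

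The before-treatment trigger is a lesser fault. In a randomised trial, a significance test of baseline balance reacts to chance and says nothing about how strongly a variable predicts outcome. A strong predictor with a modest imbalance is left out, and a weak one with a chance imbalance is put in.

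**Working it through.** The protocol gives no figure on this point, so there is none to reproduce. The fault lies in the wording; the arithmetic only shows what it could do.

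**1. Which reading of the second trigger holds.** Clinical Observation lists combined medications at the pre-treatment visit and does not repeat them at days 7, 14, 21 or 28. However, the rule sets a first clause about the period before treatment against a second about the period during it, and co-medication is the example for the second. Preservation of case report form also has medication recorded alongside treatment progress. The post-randomisation reading is the more natural one.

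**2. Before-treatment trigger.** Four factors are named: age, gender, disease type and condition. If the four tests were independent at 5%, the chance of at least one significant result under randomisation is 1 − 0.95^4 = 1 − 0.8145 = 18.5%. In a simulation (195 per arm, 5,000 trials per setting, four covariates whose joint correlation with outcome was 0.3, 0.5 or 0.7), applying the rule gave type I error of 3.7% to 4.6%. Keeping all four covariates in the model every time gave 4.2% to 5.2%.

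**3. During-treatment trigger.** From the protocol: effect size 0.28, alpha 0.05 (taken as two-sided, since sidedness is not stated), and 390/2 = 195 per arm. A t test then has power 0.788, so about 79% is the reference. The rest is assumed:

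- The outcome has SD 1, and higher values are worse.
- Latent severity U correlates r with outcome. Diathermy does not alter U, and medication has no effect of its own.
- The log-odds of medication use are U in the control arm and U − d in the experimental arm. At average severity, use is 50% in controls and 1/(1 + e^d) in the experimental arm: 40%, 31% and 23% for d = 0.4, 0.8 and 1.2.
- Medication enters the model when its own coefficient has p < 0.05. This happened in about 65% to 71% of trials at r = 0.3 and in at least 97% at r = 0.5 and 0.7.

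Results after applying the rule, 2,000 trials per cell:

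| r | d | Shift with no true effect (SD) | Type I error | Estimate when truth is 0.28 SD | Power |
|---|---|---|---|---|---|
| 0.3 | 0 | 0.003 | 6.2% | 0.280 | 78.2% |
| 0.3 | 0.4 | 0.018 | 5.6% | 0.265 | 74.5% |
| 0.3 | 0.8 | 0.028 | 5.9% | 0.248 | 67.7% |
| 0.3 | 1.2 | 0.047 | 9.2% | 0.231 | 60.9% |
| 0.5 | 0 | −0.002 | 4.0% | 0.282 | 80.6% |
| 0.5 | 0.4 | 0.036 | 7.0% | 0.249 | 70.9% |
| 0.5 | 0.8 | 0.068 | 11.5% | 0.216 | 57.8% |
| 0.5 | 1.2 | 0.097 | 15.8% | 0.186 | 44.8% |
| 0.7 | 0 | 0.001 | 4.9% | 0.278 | 81.8% |
| 0.7 | 0.4 | 0.046 | 6.9% | 0.233 | 66.7% |
| 0.7 | 0.8 | 0.091 | 14.6% | 0.186 | 48.3% |
| 0.7 | 1.2 | 0.133 | 26.5% | 0.146 | 31.6% |

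The unadjusted test in the same null runs rejected in 4.3% to 5.9% of trials, with bias near 0. The simulation error on a 5% rate is √(0.05 × 0.95/2,000) = 0.5 points, so the smallest entries cannot be told from 5%. The mechanism is that, when the experimental arm is prescribed less at equal severity, its medicated patients are sicker than the medicated controls, and adjustment makes diathermy look worse. If that arm were prescribed more, the sign would reverse.

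**The case against.** - **The unbiased comparison is still there.** An unadjusted test under intention-to-treat is planned, as is a regression on age and gender without any condition. A reader might infer that covariates enter only through the two triggers, or that the intention-to-treat comparison has been abandoned. The protocol supports neither: the triggered analysis is not said to replace the others. This limits the harm but does not remove it, because the triggered model is itself described as the efficacy comparison and can give a competing answer.
- **Which analysis is primary may be settled elsewhere.** That is commonly left to a statistical analysis plan, which is not shown, so its absence is not counted here. The during-treatment trigger is different: it is a rule the protocol states, and a later plan that followed the protocol would inherit it.
- **The baseline trigger might be thought to inflate type I error.** It does not. Adjusting for baseline variables still targets the randomised effect, and no outcome data are needed to apply this trigger. The 18.5% also assumes independent tests, and disease type and condition are probably related.
- **Prescribing may not differ by arm.** Both arms receive the national standard drug regimen, which may restrain arm-driven prescribing. With no difference in use, the simulation shows no bias. The table therefore shows what could happen, not what should be expected.

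**Conclusion.** The point stands in a limited form, as something that should be fixed. The protocol admits post-randomisation co-medication into an efficacy model, chosen by its apparent influence on the result, in a trial where the prescriber knows the arm. The estimate from that model is not the effect of assignment. Choosing baseline covariates by significance test is a minor fault: the model depends on chance, but the error rate is not raised.

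The size rests wholly on assumed values for the link between severity and outcome and for the difference in prescribing between arms. Over the non-zero differences tried, type I error runs from about 5.6% (not distinguishable from nominal) to 26.5%. The upper figure must not be read as the trial's error rate: it belongs to the triggered analysis alone, under the strongest assumptions tried.

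**What to change.** 1. Delete the during-treatment trigger from the efficacy comparison. Report combined medication by arm descriptively, or at most in an analysis labelled exploratory.
2. Replace the baseline-significance trigger with a fixed set of covariates used whatever the baseline p-values. Age, sex and the baseline 7-category score are suitable and already collected. Disease type appears only in this rule and is not among the listed pre-treatment items, so add it only if it is defined and recorded at baseline.
3. Reconcile this set with the age and gender regression already planned, so that those two factors are not handled under two different rules.

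The cost is analysis wording only, with no new data. Trial status reports recruitment complete, so the change should be dated and made before any unblinded analysis.

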**Statistics software**

Simultaneous analysis will be performed using SPSS version 26 and GraphPad prism 8.

**Treatment quality**

The quality control of this intervention was jointly controlled by the person in charge of this study and the Ethics Committee of Tongji Hospital of Tongji Medical College of Huazhong University of Science and Technology. The research work will be performed in accordance with GCP, SOP and quality control requirements. We have developed a clinical research plan and conducted GCP training for relevant researchers participating in this trial.

1) The scheme will be submitted to the Ethics Committee of Tongji Hospital affiliated to Tongji Medical College of Huazhong University of Science and Technology for approval before the trial begins.

2) According to GCP guidelines, necessary steps should be taken during the design and implementation of the study to ensure that the data collected is accurate, consistent, complete and credible.

3) Participating researchers will conduct the intervention in strict compliance with China's GCP standards, and in accordance with the clinical trial standard operating procedures (SOP), truthfully, carefully, and carefully collect and record the contents of the case report form and verify them to ensure the data's accuracy and reliability.

4) The researcher will fill in the information required by the scheme into the case report form (CRF), and the inspector will verify whether the completion is complete and accurate, and instructs the staff of the research center to make necessary corrections and additions.

5) Various instruments, equipment, reagents, standards used in these clinical trials will be inspected following strict quality standards to ensure that they work under normal conditions.

6) The statistical problems in the treatment plan are sent to a statistical expert for review and control

7) During the trial, the investigator will monitor the research process, informed consent, and correctness and completeness of the data in the case report form (CRF).

